## Abstract

**Background:**

Complex Regional Pain Syndrome (CRPS) presents as chronic, continuous pain and sensory, autonomic, and motor abnormalities affecting one or more extremities. People with CRPS can also show changes in their perception of and attention to the affected body part and sensory information in the affected side of space. Prism Adaptation (PA) is a behavioural intervention targeted at reducing attention deficits in post-stroke hemispatial neglect. PA also appears to reduce pain and other CRPS symptoms; however, these therapeutic effects have been demonstrated only in small unblinded studies. This paper describes the protocol for an ongoing double-blind, randomized, sham-controlled clinical trial that will evaluate the efficacy of PA treatment for CRPS. The secondary aims of the study are to examine the relationships between neuropsychological changes (such as spatial attention, space and body representation, and motor spatial performance) and clinical manifestations of CRPS, as well as symptom improvement.

**Methods:**

Forty-two participants with upper-limb CRPS type I will undergo 2 weeks of twice-daily PA treatment or sham treatment. The primary outcome measures are current pain intensity and CRPS severity score, measured immediately before and after the treatment period. Secondary outcome measures include the results of self-report questionnaires about pain, movement, symptoms interference, and body representation; clinical assessments of sensory, motor, and autonomic functions; and computer-based psychophysical tests of neuropsychological functions. Data are collected in four research visits: 4 weeks and 1 day before treatment, and 1 day and 4 weeks after the end of treatment. Additional follow-up through postal questionnaires is conducted 3 and 6 months post-treatment.

**Discussion:**

It is hypothesised that participants undergoing PA treatment, compared to those receiving sham treatment, will show greater reduction in pain and CRPS severity score, and improvements on other clinical and neuropsychological measures. Also, more pronounced neuropsychological symptoms are predicted to correlate with more severe clinical CRPS symptoms. This study will provide the first randomized double-blind evaluation of the therapeutic effects of PA that could be implemented as a rehabilitation method for CRPS, and will contribute to the understanding of how neuropsychological changes in body representation and attention pertain to the manifestation and treatment of CRPS.

**Trial registration:**

(27/03/2017): ISRCTN46828292 (ISRCTN - ISRCTN46828292: Treatment of complex regional pain syndrome (CRPS) with sensory-motor adaptation).

## Background

People with Complex Regional Pain Syndrome (CRPS) experience continuous pain and a range of sensory, autonomic, and motor signs and symptoms. The condition primarily affects one or more extremities, which can become swollen and present with asymmetric changes in hair, nail and skin growth, sweating, limb temperature, and skin colour. Further clinical features of CRPS include allodynia (non-nociceptive stimulation perceived as painful) and hyperalgesia (mildly noxious stimulation experienced as extremely painful), as well as motor disturbance in the affected limb (e.g., decreased range of movement, weakness, tremor, and muscle contractions [1, 2]). Although CRPS usually develops after an injury to the limb (e.g., a fracture [3]), it can also develop spontaneously [4], and the symptoms are disproportionate to any inciting trauma [2]. There is no known cause of CRPS, however, several pathophysiological mechanisms are suggested to play a role in the development and maintenance of this syndrome, including neuroinflammation, nociceptive sensitization, vasomotor dysfunction, and maladaptive neuroplasticity [1].

CRPS patients have shown reduced attention to tactile [5–7] and visual stimulation on the affected limb and in external space near it [8, 9]. These biases appear to be associated with the side of space in which the limb usually resides [6, 8] rather than a tendency to pay less attention to the affected body parts per se. These space-based attention changes resemble those found in post-stroke hemispatial neglect patients [10].

One emerging treatment for CRPS is Prism Adaptation (PA). PA is a form of a sensory-motor training used to reduce lateralised attention deficits in post-stroke hemispatial neglect. The treatment involves performing a pointing task while wearing goggles fitted with prismatic lenses that induce a lateral deviation of the visual image. Due to this visual shift, patients’ pointing initially errs in the direction of prismatic displacement. With repeated movements, pointing becomes more accurate through an adjustment of pointing movements in the opposite direction to the optical shift, indicating a realignment of the sensory-motor reference frames [11, 12]. Once the goggles are removed, a negative after-effect is observed whereby pointing movements err in the opposite direction to the earlier optical shift. Using PA to induce pointing after-effects towards the neglected side reduces post-stroke hemispatial neglect [13–21].

The apparent attention bias in CRPS patients led to investigations of whether PA could also have therapeutic effects on chronic pain, as it does in post-stroke hemispatial neglect. Results of three studies have shown that PA performed with the affected hand to produce pointing after-effects towards the CRPS-affected side reduced pain and other CRPS symptoms [22–24]. One proposed mechanism of these apparent therapeutic effects is that PA reduces pain through correcting the lateralised spatial attention bias in people with CRPS. The magnitude of spatial biases has been previously linked to the severity of pain and other clinical signs of CRPS [6, 7, 25–29]. Moreover, PA leading to the after-effects away from the affected limb appears to increase pain in CRPS [24], further supporting the role of lateralised attention effects. Another potential mechanism is that PA restores normal sensory-motor integration. Although empirical evidence to support this mechanism is limited, it has been proposed that discrepancies between motor commands and sensory feedback can contribute to pathological pain, including CRPS [24, 30–32].

However, the studies demonstrating therapeutic effects of PA in CRPS [22–24] included only small numbers of patients (13 in total across all three studies), no sham treatment conditions, and were not blinded. Thus, to date there are no sufficient grounds for implementing PA as a standard rehabilitation method for CRPS [11]. The aim of this study is to provide a robust evaluation of the effects of PA on CRPS through a double-blind, randomized-controlled trial.

### Research questions and hypotheses

#### Primary research question (RQ) and hypothesis

Is two weeks of twice-daily PA treatment more effective in reducing pain and CRPS symptom severity than an identical regime using sham prism adaptation (“sham treatment”)?

Sham prism adaptation has an identical procedure to PA treatment, except that pointing movements are performed without any optical deviation and therefore no adaptation takes place. This will allow us to dissociate the effects of the additional movement of the affected limb imposed by the treatment, to isolate the true effects of PA.

Hypothesis: There will be greater reductions in pain and CRPS symptom severity in the participants who receive PA treatment compared to the participants who receive sham treatment.

#### Secondary research questions and hypotheses

RQ 2.Are there any improvements in other clinical signs of CRPS, psychological functioning, and neuropsychological symptoms following PA treatment?

In addition to the primary outcome measures of pain and CRPS symptom severity, we aim to evaluate the effects of PA treatment on secondary outcomes (listed below) that are relevant to participants’ daily physical and psychological functioning, and for understanding the mechanisms of the therapeutic effects of PA (e.g., through establishing which neuropsychological symptoms might be affected by treatment).

Hypothesis: Compared to the sham treatment group, participants in the PA group will have a reduction in spatial attention bias (consistent with its primary applications), as well as bias in cognitive representation of space and spatially-modulated motor function; body representation distortion (see [22]); emotional disturbance; fear of movement; average pain, movement restriction, and symptoms interference; and sensory, motor, and autonomic signs of CRPS following treatment.
RQ 3.How long are any benefits sustained for after the cessation of PA treatment?

We will determine this through assessment of all primary and secondary outcomes immediately and 4 weeks after the completion of treatment, and through additional assessment of a subset of self-reported secondary outcomes at 3 and 6 months post-treatment. The time course of any improvements will be also analysed at more granular level through participants’ daily subjective ratings of pain, range of movement, and the extent to which their symptoms interfere with daily life over a period of 10 weeks.
RQ 4.Are there factors that can predict the CRPS progression over time and/or the response to PA treatment?

Finally, the current study aims to explore potential predictors of the course of the disease and therapeutic response by tracking the symptoms of the same individuals over the course of 7.5 months. We plan to identify possible markers that would account for the individual differences in the progression of CRPS over time and / or in response to PA treatment. Due to insufficient evidence to support any specific predictions and limited sample size, we will perform exploratory analyses to address this research question. Factors such as demographic characteristics, pain intensity, CRPS symptom severity, sensory, motor and autonomic functions, and the extent of neuropsychological changes will be taken into consideration.
RQ 5.Are the neuropsychological changes in CRPS related to clinical signs and symptoms of CRPS?

A secondary aim of this study is to investigate the relationships between the severity of clinical symptoms of CRPS and the extent of neuropsychological changes in spatial attention, space and body representations, and motor functions.

Hypothesis: Baseline abnormalities in perception of and attention to the affected limb and its surrounding space in participants with CRPS (compared to the perception and attention of healthy control participants) will correlate with the severity of pre-treatment clinical symptoms.

## Methods

### Design

The trial was prospectively registered [33] and Additional file 1 lists all items from the World Health Organisation Trial Registration Data Set. This study has a double-blind, randomized, sham-controlled design. The schedule of enrolment, interventions, and assessments is presented in Table 1 and consists of four in-person Research Sessions (RS), 2 weeks of twice-daily home-based treatment, and two sets of long-term postal follow-up questionnaires. After provisional eligibility assessment through a structured phone interview, 42 participants with CRPS will undergo two baseline research sessions. Two baseline assessments (RS1 and RS2) are conducted to give an indication of normal fluctuations in CRPS symptoms (or lack thereof) prior to the treatment period. This will allow us to assess whether any change over the treatment period is meaningful, that is, greater than baseline fluctuations.^1^ Research Session 1 (RS1) commences the timeline of the study at week 1 and includes in-person assessment of the eligibility criteria, informed consent, and collection of the outcome measures that are described in the “Measurements” section. Treatment allocation takes place 1–5 days before Research Session 2 (RS2), where the participants with CRPS are randomly allocated to one of the two groups of equal size: the PA treatment group or the sham treatment group. RS2 at the end of week 4 involves revisiting eligibility criteria and collecting outcome measurements. Immediately after completing RS2, the participants are instructed in how to carry out the treatment by a researcher who is not involved in any part of data collection. They then perform their first treatment under the guidance of that researcher. All other elements of the study (telephone screening, symptom assessment, experiment administration, and input of questionnaire data) are performed by researchers who are blind to the conditions that the participants have been allocated to. The treatment period spans weeks 5 and 6 of the study, where the participants perform twice-daily treatment in a self-guided manner. Outcome measurements are collected in two post-treatment assessments (RS3 and RS4) to evaluate differences in PA versus sham treatment effects, and whether any benefits of treatment are maintained at 4 weeks after treatment. The first post-treatment Research Session (RS3) takes place at the beginning of week 7 (i.e., the day immediately following the final treatment session). Research Session 4 (RS4) takes place in the beginning of week 11. Each research session is expected to last between 2 and 4 h, including breaks between the assessments. During the first 10 weeks of the study, the participants also record their self-reported daily ratings of pain intensity, range of movement, and the extent to which their symptoms interfere with daily life in a provided logbook, which will allow us to track the time course of any changes between research sessions. Long Term Follow-Up 1 at 3 months (LTFU1; week 19) and Long Term Follow-Up 2 at 6 months (LTFU2; week 31) post-treatment are conducted through questionnaires sent and returned by post. RS3 marks the primary endpoint and LTFU2 marks the secondary and final endpoint of the study.

**Table 1 Tab1:**
[figure not shown]
Schedule of enrolment, interventions, and assessments for the participants with CRPS

*RS* Research Session, *LTFU* Long Term Follow-Up (postal questionnaires only), *PA* Prism Adaptations

*Primary endpoint of the study

**Secondary endpoint of the study

***Self-reported average levels of pain, range of movement and symptoms interference with daily life in the last 24 h, rated daily on 0–10 Numeric Rating Scales

Deviations from the schedule of consecutive Research Sessions and Follow-Ups will be accepted within the following time windows: up to 2-weeks deferral of RS2 and RS4, up to 1-week deferral of RS3, up to 3-weeks deferral of LTFU1 and LTFU2. If the times that the participant can attend RS2 and RS3 are planned to be longer than 14 days apart, the participant would commence the treatment 2 weeks before RS3. If the participant already started the treatment and has to postpone RS3, they would continue the treatment until RS3.

Twenty-one healthy control participants are being recruited for a single research session to obtain normative data. They undergo testing only once and do not receive any treatment.

#### Setting of the study

All research centres and recruitment sites are located in the United Kingdom. The University of Bath is the main research centre and one of the research sites, and research sessions can also take place at the Universities of Oxford, Exeter, or Liverpool; or in participants’ homes.

### Participants

#### Eligibility criteria

##### Participants with CRPS

This study enrols both male and female individuals, who:
are willing and able to give informed consent to take part in the trial,are aged 18–80,have a diagnosis of CRPS type I based on the Budapest diagnostic research criteria [2] as assessed at RS1 and revisited at RS2,have CRPS type I primarily affecting one upper limb,have had CRPS for a minimum of 3 months at the time of RS1,and report current pain intensity ≥2 on a 0–10 Numeric Rating Scale at RS1 and RS2.

Participants are excluded from the CRPS group if they:
lack sufficient English language ability to provide informed consent,are classified as legally blind,have a history of neurological disorder (e.g. stroke, neurodegenerative disease or traumatic brain injury),have CRPS meeting the Budapest diagnostic clinical or research criteria affecting both sides of the body,^2^report that they have confirmed presence of nerve damage (CRPS type II) based on the results of nerve conduction test,have dystonia or any other physical limitation severe enough to prevent satisfactory execution of PA/sham treatment,or have a severe psychiatric comorbidity (such as schizophrenia) that in the researchers’ opinions would compromise participation in the study.

##### Healthy control participants

The inclusion criteria for healthy control participants of this trial are:
willingness and ability to give informed consent,age 18–80,and being neurologically healthy and without current or chronic pain.

Criteria that would exclude an individual from the study are:
insufficient English language ability to provide informed consent,being classified as legally blind,physical disability or injury limiting normal mobility,or a history of a neurological or severe psychiatric illness.

Each healthy control participant is matched to one participant with CRPS by sex, self-reported handedness prior to the onset of CRPS, and age (+/− 5 years).

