##### Computer-based/psychophysical tests

Six computer-based measures are used in the present study to assess the following neuropsychological functions: visuospatial attention, cognitive representation of space, spatially-defined motor function, and body representation. To test for spatial attention bias in near space, we administer versions of three tasks that have been used to measure spatial attention in hemispatial neglect: a visual Temporal Order Judgement (TOJ) task [8], a Landmark task [54], and a Greyscales task [55]. The fourth task is a Mental Number Line Bisection task, which measures the mental representation of space [56, 81]. The fifth task is a Directional Hypokinesia task, a measure of motor “neglect-like” impairment. The final computer-based task is a Hand Laterality Recognition task, which is thought to be indicative of body representation [58].

All measures presented in this section are collected in RS1-RS4 from the participants with CRPS and during a single research session from healthy control participants. Hand and side of space for all tasks are coded as affected or unaffected (for controls, the “affected” and “unaffected” hand / side is coded based on their matched participant with CRPS). Each task is preceded by a short practice session to familiarise the participant with the task. If they do not appear to follow the instructions during practice, these are explained again, and the practice is repeated.

***Visuospatial attention*** The following three computer-based tests are used to measure visuospatial attention: the visual TOJ task, the Landmark task and the Greyscales task.

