**Fig. 3 Fig3:**
[figure not shown]
Example pair of stimuli in the Greyscales task. A person who has reduced attention to the left side of space would judge the upper bar as having overall greater average darkness

***Mental representation of space*** The Mental Number Line Bisection task aims to measure spatial bias in the mental representation of space. This is based on the evidence that people implicitly represent numbers in a linear arrangement in which smaller numbers are located to the left side of space, and larger numbers are located to the right side of space [97]. The procedure is adapted from a previous study [56] in which pairs of numbers were read aloud to the participants and they were required to indicate the number that would fall midway between the two without making any calculations. The current task uses the same intervals (9, 16, 25, 36, 49 and 64) between two numbers that ranged from 2 to 98. For example, the midpoint number between 54 and 70 (16-interval) would be 62 (Fig. 4). The only deviation from the previous procedure [56] is that every pair of numbers is presented twice – once in ascending and once in descending order, to reduce response bias. There are 84 trials presented in pseudorandom order and participants’ verbal responses are inputted to the computer via the keyboard by the researcher. We subtract the subjective midpoint number from the objective midpoint number in each trial (for example, see Fig. 4), and the average score is transformed to indicate the relative bias in the mental representation of space away (negative values) or towards (positive values) the affected hand-side. A bias away from the affected side was previously found in CRPS patients on Mental Number Line Bisection [56], as well as a rightward bias in post-stroke hemispatial (left) neglect patients [81, 98–100], and a leftward bias in healthy participants (“pseudoneglect”) [56, 101, 102].

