#### Sample size and power calculation

The required sample size was calculated based on the primary outcome measure of self-reported pain [109]. A meta-analysis defined a clinically significant reduction in pain as a change of Δ = − 2 (on a scale of 0–10) [110]. The sample size required to detect a pain reduction of this magnitude between RS2 and RS3 was estimated. The risk of type I error was set at 5% and the risk of type II error was set at 10%, giving 90% power to detect a significant change in the pain. The standard deviation expected in the current study was estimated as 1.98 based on pain intensity ratings obtained by our group in recent research [8]. Given these parameters, a minimum of 42 participants with CRPS (21 per group) is required to evaluate the effects of the PA treatment on the primary outcome measure of pain. Taking into account an anticipated drop-out rate of 20%, up to 52 participants with CRPS will be enrolled in order to obtain a total of at least 21 complete datasets for RS1-RS4 per treatment group. To provide normative data, 21 healthy (pain-free) control participants will be recruited.

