#### Baseline neuropsychological symptoms and their relationships with the clinical symptoms of CRPS (RQ5)

We will conduct a series of contrasts to compare mean age, proportion of males and females, and proportion of left- and right-handed individuals between participants with CRPS in RS1 (total CRPS sample, regardless of subsequent treatment allocation) and healthy controls. Participants’ mean scores on self-report questionnaires and clinical assessments in RS1 will also be compared between the two groups. Specifically, we will conduct contrasts to compare participants with CRPS and healthy controls groups on the BPDS and Profile Of Mood States scores; the hand laterality indices (current for healthy controls, and handedness before CRPS for the participants with CRPS); limb temperature asymmetry and hands size difference (affected – unaffected), grip strength and ΔFTP ratios (affected/unaffected), MDT, MPT, two-point discrimination threshold ratios, and mean allodynia score on the affected side.

To test whether the participants with CRPS in RS1 show visuospatial attention bias compared to healthy controls, we will use four separate contrasts. Specifically, we will conduct four between-group comparisons of the following variables: PSSs in the TOJ task, PSEs in the Landmark task, attention bias scores in the Greyscales task, and bias scores in the MNLB task.

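### RQ5 compares 21 individually matched controls with all 42 to 52 CRPS participants without adjustment; adjusting for coded affected side and the matching factors would be a cheap improvement

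*Protocol article*

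**What the plan says.** The control group is fixed at 21. The Design section states: "Twenty-one healthy control participants are being recruited for a single research session to obtain normative data". The sample size section repeats the number: "To provide normative data, 21 healthy (pain-free) control participants will be recruited".

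Under Healthy control participants, the matching is individual: "Each healthy control participant is matched to one participant with CRPS by sex", and also by pre-CRPS handedness and age (within 5 years). Affected side is not a matching factor. It is inherited instead: for the computer-based tasks a control's "side is coded based on their matched participant with CRPS", and the sensory tests and the BPDS follow the same rule.

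The RQ5 analysis section defines the CRPS group as the "total CRPS sample, regardless of subsequent treatment allocation". The sample size section puts that sample at a minimum of 42, with up to 52 enrolled. The RQ5 tests are between-group contrasts and ANOVAs, with neither pairing nor covariates mentioned. Age, sex and handedness are to be compared between the two groups; no comparison of affected side is stated. For RQ1, by contrast, the article does name covariates that may be used if the arms differ at baseline.

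The Mental Number Line Bisection paragraph reports a bias away from the affected side in CRPS "and a leftward bias in healthy participants".

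**The concern.** One-to-one matching protects a comparison of the matched sets. Here 21 controls resemble 21 index participants, but the comparison group also contains the other 21 to 31, so the matching does not carry over automatically to the groups compared.

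Affected side deserves most attention because several RQ5 outcomes are recoded from left/right to affected/unaffected. If healthy people lean leftward by b on a task, a control coded left-affected scores +b and one coded right-affected scores −b, so the recoded group mean depends on the left/right mix. The article treats laterality as relevant elsewhere: affected arm and dominant hand are separate minimisation factors in Table 2, and the grip-strength criteria allow for normal dominance differences.

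RQ5 also steers later work. RQ4 first considers the measures that differ most from controls, and the correlation and regression analyses depend on which outcomes differ significantly. Both are declared exploratory, so what is at stake is the reliability of secondary and exploratory findings.

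**Working it through.** **Inputs from the article.** Controls 21; CRPS sample N = 42 minimum, up to 52 enrolled; pain difference 2, SD 1.98, type I error 5%, power 90%, drop-out 20%. The share left-affected and the size of b are not given, so they are assumptions below.

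**Reproducing the planned sample.** A two-sided normal approximation with difference 2, SD 1.98, alpha 0.05 and 90% power gives 21 per group, 42 in total, as stated. For drop-out, 42/0.8 = 52.5, against 52 stated. The 42-to-52 range can be taken at face value.

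**Share without a match.**
- N = 42: (42 − 21)/42 = 21/42 = 50%.
- N = 52: (52 − 21)/52 = 31/52 = 60%.

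**Effect of a gap in side mix.** With share left-affected q, the recoded mean from normal bias alone is b·q − b·(1 − q) = b(2q − 1). Two groups whose shares differ by p therefore differ by 2pb. A gap of 10 percentage points gives 0.2b; 20 points gives 0.4b.

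**How large a gap chance produces.** Assume the 21 index participants are a random subset and half the sample is left-affected. The SD of the spurious difference is 2b·√[0.25(1/21 − 1/N)] = b·√(1/21 − 1/N):
- N = 42: 0.154b.
- N = 52: 0.168b (0.169b by simulation).

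If 30% to 50% are left-affected, the hypergeometric calculation gives an SD of about 7 to 9 percentage points for the gap, and an 18% to 26% chance of a gap of at least 10 points. The mean gap is zero.

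**Whether this inflates false positives.** An unpaired test already carries side variation in each group's SD. For the side component its standard error allows b·√(1/21 + 1/42) = 0.267b, more than the 0.154b that occurs, because controls borrow their sides from the same sample. Simulation with no true difference, half left-affected and b in between-person SD units gives these rejection rates at a nominal 5%:

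| N | b = 0.3 | b = 0.5 | b = 1 |
|---|---|---|---|
| 42 | 4.4% | 3.6% | 1.6% |
| 52 | 4.5% | 3.8% | 2.1% |

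The test is conservative. To put the imbalance in scale: at b = 0.5 SD and N = 42 its SD is 0.5 × 0.154 = 0.077 SD, against a standard error of √(1 + 0.25) × 0.267 = 0.30 SD.

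**What adjustment recovers.** Adding coded side as a covariate brings type I error back to about 5%. At N = 42, b = 0.5 SD and an assumed true difference of 0.7 SD, power rises from about 63% to about 72%; a repeat run agreed within two percentage points.

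**If the 21 are not a random subset.** The shift 2pb then has a non-zero expectation. The article gives no figure for p, so its size cannot be stated.

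**The case against.** The strongest reply is that nothing is wrong with the comparison as such. Controls are there to supply normative data, and an unpaired 21-versus-42 comparison has more power than 21 versus 21: 84% against 72% at an assumed standardised difference of 0.8. This stands. Three of the four relevant factors are also compared in the groups actually analysed. That stands too, although no action is attached to those comparisons and affected side is left out.

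A reader might infer that the affected-side coding is unbalanced between groups. The documents do not support this: balance is not guaranteed, but the 21 could mirror the full sample by selection or by chance. A reader might also infer that side mix manufactures false CRPS deficits. Under random selection the simulation shows the reverse; systematic bias needs an unrepresentative 21, for which the article offers no evidence either way. Finally, the leftward bias is stated for number-line bisection, so applying a similar b to other tasks is an assumption.

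It may seem natural to repair the mix by relabelling the coded side of controls already tested. The procedures rule this out. Controls answer the BPDS about one limb only, sensory testing always starts on the unaffected limb, and the Landmark, Greyscales and Hand Laterality responses use the unaffected hand. Relabelling would confound side with test order and response hand.

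**Conclusion.** The concern holds as a cheap improvement, not as an error that invalidates RQ5. At the planned sizes, 50% to 60% of the CRPS sample has no matched control, and the mix of coded affected side is neither ensured nor checked against the sample analysed.

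With effectively random index participants, the consequence is lost precision: type I error of about 1.6% to 4.5% for b between 0.3 and 1 SD, and about nine points of power in the setting shown. With an unrepresentative 21, the group difference is biased by 2pb. These sizes rest on an assumed share left-affected (50% in the simulations, 30% to 50% in the gap calculation) and on assumed values of b and of the true difference. The randomised PA-versus-sham comparison is untouched.

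**What to change.** - In the RQ5 CRPS-versus-control comparisons, at least for side-recoded outcomes, prespecify coded affected side (left/right), age, sex and pre-CRPS handedness as covariates.
- Report the affected-side mix in both groups beside the planned comparisons of age, sex and handedness.
- Add a 21-versus-21 matched-pair sensitivity analysis, in which coded side is identical by construction.
- For controls not yet tested, choose index participants so that their affected-side mix follows the full CRPS sample.
- Leave the coded side of controls already tested as it is.

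All four covariates are already collected and no further controls are needed. The cost is a few degrees of freedom and some added text in the RQ5 analysis section.
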